**Figure 1 F1:**
[figure not shown]
**Study design**.

The study comprises two different follow-up phases; one retrospective and one prospective (ambispective design). The retrospective phase for each patient started from the index event, which occurred a maximum of 12 months and minimum of 3 months before Time 0, and ended when the patient signed the informed consent form. Information from medical records related to the patient and their disease during that period (i.e. retrospective information - from index event to inclusion) was recorded in the electronic case report form (eCRF) at the inclusion visit. The prospective phase started when the first patient signed the informed consent form and will end when the last patient included in the study attends their final visit. Data for prospective analysis are collected as described at all visits (including the inclusion visit). All throughout the prospective phase, the required information will be recorded in the eCRF and the questionnaires completed every time the patient attends the psychiatrist's office (unless otherwise stated). The psychiatrist will schedule visits according to real-life clinical practice. No interventions, extra procedures, or extra visits will be required for the purpose of the study.

The study design means that patients will spend variable amounts of time in the study depending on the date of signing the informed consent form, the length of the enrolment period, and the date of their index episode. The minimum time in the study is 12 months and the maximum 27 months, considering the retrospective and prospective phases, and the 6 month enrolment period together (Figure 1).

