### Patient population

Each investigator identified all patients with at least one mood event in the 12 months prior to the beginning of the study (Time 0), except for those whose index mood event occurred in the 3 months before the study start.

The aim of the study is to achieve systematic inclusion of patients, therefore, where possible, every eligible patient identified at each of the study centres was invited to participate. The main exceptions were at those sites that saw a high number of eligible patients during the recruitment period. At these sites, investigators were allowed to recruit a representative sample using an electronic application, which makes selections by simple randomisation, in order to avoid any type of selection bias.

Patients aged ≥ 18 years, with a diagnosis of BD type I or II (DSM-IV-TR [1]) in any phase of the disorder and who had at least one mood event (depression, mania, hypomania or mixed) according to the DSM-IV-TR definitions during the 12 months prior to the beginning of the study were eligible for recruitment, except for those starting the index mood event less than 3 months before Time 0, subject to their providing informed consent. However, those patients starting the index mood event more than 3-months before Time 0 were eligible even if the index event was not resolved, or if the index event had resolved and they subsequently initiated another event.

Patients not eligible to participate in the study were those participating in an interventional clinical study and any patients unable to complete Patient Reported Outcomes questionnaires.

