### Measurements

The WAVE-bd study aims to provide a wide-ranging picture of BD management practices, and impact on patients, caregivers and healthcare resource use across a range of countries. For this reason, several measuring instruments are being employed to maximise the types of data collected. All instruments have been validated before the study start, including linguistic validation where needed. In all cases, the scales were also psychometrically validated, at least in the original language. Information regarding demographics (sex, race, age, educational level, professional status, degree of disability, degree of independence or co-residence), alcohol and other substance abuse, medical history, disease characteristics (date of first diagnosis, type of BD, family history of psychiatric diseases, episodes during the last 12 months, presence of psychotic symptoms, hospital admissions, and suicide attempts), treatments received (drug, schedule and dose, and whether the patient received psychologist or group therapy), healthcare resources use, and clinical outcomes will be collected throughout the study (Table 2).

**Table 2 T2:** Study plan and assessments

Time	First visit*	Each other visit	Last visit
Site information	X		
Patient demographics	X		
Medical history	X		
Disease characteristics	X		
Treatment information	X	X	X
Healthcare resources consumption	X	X	X
Clinical outcomes	X	X	X
Adherence to treatment	X	X	X
Quality of life	X	X	X
Functioning	X	X	X
Caregiver demographics	X**		
Caregiver burden	X**		

* First visit: the visit when the patient signs the informed consent form.

** If the caregiver does not attend this visit, the information will be collected at the next visit that the caregiver attends. This information will be collected (if the caregiver consents) only once during the study period for each caregiver. In the event that the caregiver does not attend any visits, this information will not be collected.

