### Statistical analyses

Descriptive statistics will include frequency tables (n, mean, median, standard deviation, minimum and maximum for continuous variables and n, frequency and percentage for categorical values). For the population estimation of the variables, the two-sided 95% confidence interval will be obtained.

In order to assess the association of patient characteristics (including functioning and quality of life status) and clinical management (an independent variable) with clinical outcome variables (clinical evolution, mood events, treatment-related events, suicide attempts, variation in scales), logistic and general linear models have been planned. Interest will focus separately on the management differences between the models or groups of models. Model-based point estimates of odds ratios and corresponding 95% confidence intervals will be reported. P-values will be reported for the comparison between different treatments. Since visit-by-visit information from the study index event is being collected, there will be data on patient status during the whole study period. Therefore, it will be possible to analyse data, relative to the time of mood event initiation.

Cox models for survival outcomes, and mixed models for longitudinal data using country as indicator variables, adjusted for age and gender, have been planned in order to investigate differences in clinical outcomes and related factors between countries. A descriptive analysis has been planned to assess factors related to consumption of healthcare resources and caregiver burden, according to caregiver-reported outcomes.

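### The planned between-treatment P-values can reflect why and when a treatment was prescribed, because nothing in the plan places treatment before outcome or accounts for mood state at treatment choice

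*Protocol article*

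**What the plan says.** All references are to the protocol article.

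- **Models.** Statistical analyses relates "clinical management (an independent variable) with clinical outcome variables", and for this purpose "logistic and general linear models have been planned". The outcomes include mood events, suicide attempts and change in scale scores. Odds ratios with 95% confidence intervals are to be given, and "P-values will be reported for the comparison between different treatments".
- **Covariates.** The same sentence covers the "association of patient characteristics (including functioning and quality of life status"; these characteristics therefore belong to the same modelling exercise. The only adjustment set spelled out belongs to the Cox and mixed models that compare countries, "using country as indicator variables, adjusted for age and gender".
- **Timing.** The section adds that visit-by-visit data would allow analysis relative to the start of a mood event. This is offered as a possibility. No treatment start point is given.
- **Treatment.** Study design states that "No interventions, extra procedures, or extra visits will be required for the purpose of the study". Measurements lists "treatments received (drug, schedule and dose, and whether the patient received psychologist or group therapy" among the data collected, and Table 2 has treatment information recorded at the first, each other and last visit.
- **Patients.** Under Patient population, adults with BD I or II are eligible "in any phase of the disorder".

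**The concern.** In routine care the psychiatrist chooses and changes treatment in the light of the patient's state. The article does not say so, but it is a safe inference: treatment is not assigned by the study, and every patient enters with a recent mood event. Two problems follow for a comparison between treatments.

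1. **Indication.** Treatments used for different polarities or severities go to patients with different outlooks. An outcome difference can then arise with no difference in treatment effect.
2. **Reverse timing.** A logistic model of whether an event occurred has no built-in order in time. Unless exposure is required to precede the event, a drug started because of an episode can count as exposure for that episode.

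The models that handle timing more naturally, Cox and longitudinal mixed models, are assigned to country differences. At stake is the stated objective of establishing factors associated with management patterns and outcomes. With about 3000 patients, modest bias of this kind is often statistically significant.

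**Working it through.** **The plan's own figure.** No figure in the article concerns treatment comparisons. The one computed design figure, 370 per country, is for estimating a proportion. It is reproduced by a continuity-corrected precision formula: 1.96 × √(0.35 × 0.65 / 370) + 1/(2 × 370) = 0.0486 + 0.0014 = 0.0500. It neither supports nor weakens the present point.

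**Inputs for the illustrations.** From the article: 35% of patients expected to have episodes in one year (Sample size) and 2965 patients enrolled (Discussion and conclusions). Everything else is assumed. The drug has no effect throughout, and severity is left unadjusted.

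**(a) Indication.** Let 40% of patients be sicker, with event risk r1 against r0 in the rest. The overall risk is held at 35%, so r1 = (0.35 − 0.6 r0)/0.4. The drug goes to a fraction u1 of sicker and u0 of other patients.

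- Share treated: t = 0.4 u1 + 0.6 u0
- Risk in treated: (0.4 u1 r1 + 0.6 u0 r0)/t
- Risk in untreated: (0.4(1−u1) r1 + 0.6(1−u0) r0)/(1−t)
- z = risk difference / √[0.35 × 0.65 × (1/(2965 t) + 1/(2965(1−t)))]

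| u1 | u0 | r1 | r0 | Risk treated | Risk untreated | OR | z | Chance of P < 0.05 |
|---|---|---|---|---|---|---|---|---|
| 0.5 | 0.3 | 0.425 | 0.30 | 0.366 | 0.340 | 1.12 | 1.41 | 29% |
| 0.6 | 0.3 | 0.500 | 0.25 | 0.393 | 0.319 | 1.38 | 4.16 | 99% |
| 0.7 | 0.3 | 0.575 | 0.20 | 0.428 | 0.283 | 1.89 | 8.25 | about 100% |

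**The other direction.** Suppose the drug is given mainly to the less sick: u1 = 0.3, u0 = 0.5, r1 = 0.50, r0 = 0.25. Then t = 0.12 + 0.30 = 0.42. Risk in treated is (0.060 + 0.075)/0.42 = 0.321, and in untreated (0.140 + 0.075)/0.58 = 0.371. The OR is (0.135/0.285)/(0.215/0.365) = 0.80, so the same null drug looks protective.

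**(b) Reverse timing.** Suppose exposure means any use, 30% of patients use the drug beforehand, and a fraction f of previously untreated patients with an event start it because of that event. Exposure is 0.3 + 0.7f among patients with an event and 0.3 among the rest, so OR = (0.3 + 0.7f)/(0.3(1 − f)).

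- f = 0.1: 0.37/0.27 = 1.37
- f = 0.3: 0.51/0.21 = 2.43

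**Do the named covariates close the gap?** Measurements places the functioning (FAST) and quality-of-life (EQ-5D) assessments in the prospective phase. The index event began at least three months before Time 0, so treatment of it may already have been under way when these scales were first completed. Change in scale scores is also an outcome. Neither instrument records mood state when treatment was chosen.

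**Could the data order treatment and mood?** Largely yes. The life chart rates mood daily and lists medications by month, in both phases. The gap lies in the analysis described rather than in the data.

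**The case against.** Several stronger readings are tempting, and the article does not support them.

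- *The treatment models are unadjusted.* A reader might infer this because age and gender are named only for the country models. But patient characteristics sit in the same modelling exercise, and Measurements lists BD type, psychotic symptoms, episodes, admissions and suicide attempts among the data. Which of these are entered, and whether jointly, is not stated.
- *Exposure is any use over the whole follow-up.* No such definition is given. Illustration (b) shows what happens if it is used, not what the plan says.
- *Drugs given to sicker patients will look harmful.* Direction and size depend on prescribing patterns that the article does not report, and the reversed case above shows apparent benefit.
- *The missing covariate list is itself a defect.* An article commonly leaves such detail to the full protocol or analysis plan.

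It can also be said that the analysis is framed as association, that the study is sized for description, and that a P-value in an observational model is not an error in itself. All of that is fair. The Discussion does lean further, since it expects the study to show what follows from the management patients receive. It discusses selection and misdiagnosis, but not confounding by indication.

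What remains is a stated method, not merely an absence: the article commits to between-treatment P-values from models with no built-in time order, for treatments that routine care can change, while the time-to-event and longitudinal models serve another question.

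**Conclusion.** The concern holds in a limited form. As described, the between-treatment P-values can reflect indication and reverse timing as well as any treatment effect, and the bias can run in either direction. For a drug with no effect, the illustrations give odds ratios of about 1.1 to 1.9 from indication when sicker patients are treated more often, 0.80 in the reversed case, and 1.4 to 2.4 if treatment started after an event counts as exposure. These sizes rest on assumed severity mixes, prescribing rates and unadjusted severity. The 35% is a one-year figure used here as the overall risk. They show that the mechanism can matter at this sample size; they do not estimate the bias in this study.

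**What to change.** For comparisons between treatments:

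1. Count only treatment recorded, on the life chart or at a visit, before the outcome event. One way is a lagged time-varying covariate in a Cox model. This would be an added analysis, because the planned Cox models address countries.
2. Stratify by, or adjust for, index-event polarity and BD type.
3. Adjust for psychotic symptoms, admissions, suicide attempts and episodes dated before the exposure window. Do not use events after the index event as baseline history. The 12-month episode count taken at the first visit can overlap the retrospective follow-up, so adjusting for it may condition on the outcome.
4. Report estimates with 95% confidence intervals as associations, and drop between-treatment P-values from any logistic model that does not place treatment before outcome.

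The cost is analysis wording and extra programming, fewer patients per comparison and wider intervals. Treatment timing may be resolved only to the visit or month, and the article does not say whether all the history items are dated. Some time-varying confounding will remain.

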### Sites and investigators

Since the type of site is a variable that might influence the management of patients with BD and the profile of patients attending each type of site may be different, it was necessary to select different types of sites to obtain a representative sample. Generally, patients with BD are seen in mental health centres, clinics, private settings, hospitals or specialised units. Since this distribution varies from one country to another, the study centre selection process had to be adapted locally.

Selection of participating sites was based on the percentage of patients that attend different types of sites in each country, thus ensuring that patients attending one specific site type are not over-represented in the study sample (Table 1). These percentages were obtained either from the literature or from expert panels from each participating country.

**Table 1 T1:** Patient recruitment by country and type of study centre

Country	Site type	Patients per site type (%)	Total patients enrolled
Austria	University hospital	16	20
	Private practice	65	81
	General hospital	19	24

Belgium	Clinics	46	190
	Private practice	31	129
	General practitioner	23	95

Brazil	Public hospital	88	146
	University hospital	12	20

France	Hospital/clinics	49	247
	Private practice	51	260

Germany	University hospital	27	59
	Community hospital	21	46
	Private practice	52	114

Portugal	Hospital	24	123
	Private practice	57	295
	Mental health clinic	19	98

Romania	Ambulatory	37	68
	Hospitals	63	115

Turkey	Private practice	39	151
	University hospital	42	162
	State hospital	18	70

Ukraine	Mental health clinic	90	199
	Private practice	10	22

Venezuela	Private practice	33	76
	Public hospital	67	155

The number of participating investigators is sufficient to ensure: 1) that there is a representative sample of the whole psychiatrist population in each country; and 2) inclusion of a sufficient number of patients to provide the required sample size calculated for the study. No other criteria were applied to selection and inclusion of investigators, in order to avoid any selection bias.

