Approximately 250 study centres in 10 countries are participating in the study. Based on the criteria described above, target percentages of patients recruited by each type of study centre were devised to reflect management practices in each of the participating countries (Table 1). The study data will be able to provide a global perspective on comparisons between public *vs *private care, academic hospital *vs *standard hospital care, and hospital *vs *non-hospital care.

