### Sample size

The sample size was calculated in order to ensure that the study obtains meaningful data for descriptive purposes of general clinical management and clinical outcomes at a country level. The main outcome used in the sample size calculation was the proportion of episodes in 1.5 years and the goal was to estimate this proportion in the study population. The minimum number of patients required was estimated, based on an expected proportion of patients with episodes in one year of 35%, assuming an alpha = 0.05, power = 0.80 and a precision of 0.05 (with a 95% confidence interval). The estimated sample size was 370 patients per country (or 400 if it is assumed that approximately 10% will be lost to follow up). Fewer patients per country would provide information on the proportion of episodes with a precision less 5%. It was estimated that approximately 3,200 patients across different countries would be included in the study, but that this number might vary depending on the number of participating countries and sample size in each.

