All of the studies described above were based on low rates of recruitment from the eligible population. A total of 3188 randomly selected patients were invited to participate in the WAVE-bd study. Of these, 2965 (93%) accepted the invitation to participate and provided written informed consent. The other 7% of patients screened declined to participate and will not be included in the analysis. The systematic approach to inclusion of patients in the WAVE-bd study and stratification by type of study centre to reflect local practice, combined with the 93% patient acceptance rate, leads us to believe that the study population avoids selection bias and is truly representative of the overall global population with unstable BD. Consequently, the investigators believe that the study promises to provide psychiatrists with reliable and up-to-date information about the factors associated with different management patterns of BD on a global scale.

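### Patients are nested in about 250 centres, but no allowance for centre is stated in the country models, the confidence intervals or the 370-per-country sample size

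*Protocol article*

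**What the plan says.** All references are to the Protocol article.

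- **Sites and investigators.** "Approximately 250 study centres in 10 countries are participating in the study". Sites were chosen by type within each country because "the type of site is a variable that might influence the management of patients with BD". The same section adds that the profile of patients may differ between types of site.
- **Discussion and conclusions.** 3188 patients were invited. "Of these, 2965 (93%) accepted the invitation to participate and provided written informed consent". The counts in Table 1 also sum to 2965.
- **Statistical analyses, descriptive part.** "For the population estimation of the variables, the two-sided 95% confidence interval will be obtained". The variance method is not given.
- **Statistical analyses, association models.** Logistic and general linear models relate patient characteristics and clinical management to outcome. Odds ratios with 95% intervals are to be reported, and P-values are announced for treatment comparisons. No closed list of covariates is given.
- **Statistical analyses, country comparisons.** Cox models and "mixed models for longitudinal data using country as indicator variables, adjusted for age and gender". The random effects of the mixed models are not listed.
- **Sample size.** 370 patients per country are to estimate a proportion expected to be 35% to within 0.05 with 95% confidence, or 400 allowing for about 10% loss. For the total, "It was estimated that approximately 3,200 patients across different countries would be included in the study".

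No part of the article mentions a centre effect, a frailty, a robust variance, an intraclass correlation or a design effect.

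**The concern.** Patients enter through centres, so two patients from one centre share prescribers, local habits, referral patterns and, for the clinician-rated life chart, often the rater. The article's own reason for choosing sites by type is that management and case mix vary with the setting. Outcomes within a centre should therefore be expected to correlate to some degree.

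Each centre lies in one country and belongs to one site type. Country and site type thus vary only between centres, and contrasts on them take the full effect of the correlation. Random or complete selection of patients within a centre protects against selection bias but does not remove it. If the stated covariates are all that enters the country models, and the intervals treat patients as independent, the precision reported for each country would be overstated. Differences between countries or care settings could then be declared too readily. Describing and comparing countries is a main purpose of the study.

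**Working it through.** **Inputs from the article.** About 250 centres; 2965 patients enrolled (about 3,200 planned); p = 0.35; half-width d = 0.05; 95% confidence; n = 370 per country.

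**Assumptions.** The article gives no intraclass correlation (ICC) and no number of centres per country. The ICC is taken as 0.01, 0.02, 0.05 or 0.10, meaning the correlation left within a country. The overall mean centre size is assumed to apply within a country.

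**Step 1: reproduce the 370.** Under simple random sampling, n = 1.96² × 0.35 × 0.65 / 0.05² = 349.6. The continuity correction, (n/4) × (1 + √(1 + 2/(n d)))², gives 369.3, hence 370. The stated 80% power plays no part: a one-sample test with that power would need about 698 to 726. The figure is thus fully explained by independent sampling. Even if the whole step from 349.6 to 370 were read as a clustering allowance, the factor is 370/349.6 = 1.058, which covers an ICC of only 0.058/10.86 = 0.005.

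**Step 2: design effect.** Mean centre size m = 2965/250 = 11.86, and DE = 1 + (m − 1) × ICC.

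**Step 3: consequences at n = 370.** Half-width = 1.96 × √(0.2275 × DE / 370), which is 4.9 points at DE = 1. True error of a nominal 5% test of a between-centre contrast = 2 × (1 − Φ(1.96/√DE)). Coverage of a nominal 95% interval is one minus that. Patients needed = 370 × DE.

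| Assumed ICC | DE | Width ratio √DE | Half-width (points) | Coverage | True error | Patients needed |
|---|---|---|---|---|---|---|
| 0.01 | 1.11 | 1.05 | 5.1 | 93.7% | 6.3% | 411 |
| 0.02 | 1.22 | 1.10 | 5.4 | 92.4% | 7.6% | 451 |
| 0.05 | 1.54 | 1.24 | 6.0 | 88.5% | 11.5% | 571 |
| 0.10 | 2.09 | 1.44 | 7.0 | 82.5% | 17.5% | 772 |

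Portugal enrolled the most patients (123 + 295 + 98 = 516). At ICC 0.05 its half-width is 1.96 × √(0.2275 × 1.543 / 516) = 5.1 points, so at that ICC no country reaches ±5.

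**Step 4: sensitivity.** With the planned 3,200 patients, m = 12.8 and DE is 1.12, 1.24, 1.59 or 2.18. Unequal centre sizes raise it: with DE = 1 + ((1 + CV²) m − 1) × ICC, an assumed coefficient of variation of 0.5 to 1.0 gives 1.69 to 2.14 at ICC 0.05.

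**Step 5: which contrasts are affected.** A small simulation ignored centre (linear outcome, 50 centres of 12 patients, 4000 runs, nominal 5%). It gave these rejection rates under no effect:

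| Contrast | ICC 0.01 | ICC 0.05 | ICC 0.10 |
|---|---|---|---|
| Varies only between centres | 6.9% | 11.2% | 18.6% |
| Balanced within centres | 4.5% | 5.0% | 4.1% |
| Treatment share varies moderately between centres | 4.9% | 6.4% | 7.4% |

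The first row agrees with the formula. The second shows no inflation.

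**The case against.** The strongest reply is that a journal article condenses the plan. The random effects of the mixed models, a frailty or robust variance for the Cox models and the variance method of the intervals are usually settled in the full protocol or analysis plan, which is not shown. Mixed models have random effects by definition, and nothing says that centre is left out. This stands as far as it goes, so the point has to be conditional. It does not dispose of the point, because the article names the adjustment variables of the country models without centre, and its sample size rests on independent patients.

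Three stronger readings are tempting, and the article supports none of them:

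- **That every model carries only country, age and gender.** That list belongs to the Cox and mixed models. The logistic and linear models are described separately.
- **That site-type and country P-values are planned and will be wrong.** P-values are announced for treatments only. Site-type comparisons are offered as something the data can provide, with no test named. The error rates above apply to such tests if they are made.
- **That treatment P-values are too small in general.** Treatment is recorded per patient and can vary within a centre. Step 5 shows inflation only as far as prescribing clusters by centre.

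It is also fair to say that the size depends on an ICC the article does not give, and that at 0.01 the effect is small. Including site type in a model would absorb part of the correlation. The design-effect formula is for a mean or proportion, so for the Cox and longitudinal models it is a guide only.

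**Conclusion.** The point holds in conditional form. As described, no analysis names a term for centre, and the ±5 points at 370 per country holds only if patients within a centre are independent. Unless centre is modelled, country-level intervals would be too narrow by a factor of 1.05 to 1.44, and between-centre contrasts correspondingly too precise. This rests on an assumed ICC of 0.01 to 0.10 and on the overall mean centre size applying within each country. The sample-size part is the firmest, because the 370 can be reproduced. For the models, the article leaves centre handling unstated rather than excluding it. Treatment comparisons are a lesser matter. The change is worth making because country description and comparison are central to the study and the remedy is simple.

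**What to change.** - Add a random centre effect to the mixed and general linear models. It should be random, not fixed, because fixed centre effects would absorb the country indicators.
- Use a shared centre frailty or a centre-robust variance in the Cox models.
- Use centre-clustered standard errors in the logistic models and for the country-level 95% intervals. With 250/10 = 25 centres per country on average, and probably fewer in the smallest countries, apply a small-sample correction to clustered variances within a country.
- Report the intraclass correlation for the main outcomes.
- Restate the ±5 points in the sample-size section as holding only without centre clustering, and show the half-widths for a range of correlations. Recruitment is complete, so the numbers themselves cannot be changed.

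**Cost.** Analysis wording and wider intervals. Patients were recruited through identified centres and site information is recorded at the first visit (Table 2), so no new data should be needed.
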